### Serious adverse events (SAEs)

A serious adverse event is any untoward medical occurrence or effect that

- results in death;
- is life threatening (at the time of the event);
- requires hospitalisation or prolongation of existing inpatients’ hospitalisation;
- results in persistent or significant disability or incapacity;
- is a congenital anomaly or birth defect; or
- any other important medical event that did not result in any of the outcomes listed above due to medical or surgical intervention but could have been based upon appropriate judgement by the investigator.

An elective hospital admission will not be considered as a serious adverse event.

The investigator will report all SAEs to the sponsor without undue delay after obtaining knowledge of the events.

The sponsor will report the SAEs through the web portal *ToetsingOnline* to the accredited METC that approved the protocol, within 7 days of first knowledge for SAEs that result in death or are life threatening followed by a period of maximum of 8 days to complete the initial preliminary report. All other SAEs will be reported within a period of maximum 15 days after the sponsor has first knowledge of the serious adverse events.

## Follow-up of adverse events

All AEs will be followed until they have abated, or until a stable situation has been reached. Depending on the event, follow up may require additional tests or medical procedures as indicated, and/or referral to the general physician or a medical specialist. SAEs need to be reported till end of study within the Netherlands, as defined in the protocol.

# STATISTICAL ANALYSIS

## Primary study parameter(s)

Statistical analyses will be performed by SPSS statistical analysis software. Normality of the data will be assessed by a Kolmogorov–Smirnov test. Data transformation will be done if the data is not normally distributed. The primary analyses of studied primary parameters will be performed between the baseline and endpoint intervention by analysis of one-sample t-test, or chi-square test. If the data is not normally distributed and data transformation is not possible, the Mann-Whitney test will be used. Further associations will be assessed with Pearson rank correlation test / Pearson chi-square test.

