# STUDY DESIGN

This study is designed as an intervention study in which subjects will follow the 12-week exercise intervention. Subjects will receive instructions for a high-intensity aerobic interval training (HI) (described below). Dietary intake will remain unchanged. The first part of the study is conducted with 15 subjects. This is followed by an interim analysis and based on the results of this analysis, the intervention will be extended with another 15 subjects based on approval by the IRB. The study design is presented in figure 1.

Complementary study

Baseline

Mid-intervention

Final intervention

Interim analysis

Diagnosed NAFLD

(5.5 % > liver fat)

BMI < 40 kg/m^2^

18–70 years of age

n=15

Ergospirometry test

Anthropometrics

Food records

REE

Oral swab

Stool and urine samples

MRI and MRS

Blood samples

Liver, adipose tissue and muscle biopsies

Ergospirometry test

Anthropometrics

Food records

REE

Oral swab

Stool and urine samples

MRI and MRS

Blood samples

Liver, adipose tissue and muscle biopsies

Body weight

Food records

Oral swab

Stool samples

Blood samples

Exercise intervention – pilot study

Screening

Week 0

+/- 3 week

Identical to pilot study,

recruitment of

additional subjects

+/- 3 months

Continous glucose monitoring

Continous glucose monitoring

Week 12

+/- 3 week

Week 6

+/- 2 week

Figure 1 Overview of the study design with the main procedures that will be performed during the 12-week exercise intervention.

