## Sample size calculation

Based on hepatic PNPLA3 expression that is twice as high in steatosis patients compared to healthy obese subjects (Aragonès et al., 2016). To detect a 25% reduction in PNPLA2 expression upon 12 weeks exercise course, we expected to need a group sample size of 28 (2sided chi- square test with a desired alpha of 0.05 and a desired power of 0.8). Assuming around 10 % of dropouts in this trial, a final sample size of 30 is required. Based on the suggestions of the IRB we will start with inclusion of 15 subjects and study changes in liver gene RNAseq including PNPLA3 gene liver expression upon exercise (Aragonès et al., 2016). Based on those findings, we will validate our power calculation above and see if the number of 30 subjects is indeed needed.

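### A low-power Kolmogorov–Smirnov pre-test of unstated version chooses the analysis scale at 15 to 30 subjects, although the planned effect is a percentage change

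*Protocol*

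**What the plan says.** Protocol section 8.1 sets out a sequence. The software is named ("Statistical analyses will be performed by SPSS statistical analysis software"), then the gate: "Normality of the data will be assessed by a Kolmogorov–Smirnov test. Data transformation will be done if the data is not normally distributed". The primary comparison is made "between the baseline and endpoint intervention by analysis of one-sample t-test, or chi-square test". The last step is a fallback: "If the data is not normally distributed and data transformation is not possible, the Mann-Whitney test will be used". Section 8.2 refers the metabolome, transcriptome and microbiota data back to the same approach.

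The target effect is in section 4.4: "To detect a 25% reduction in PNPLA2 expression upon 12 weeks exercise course". (The gene is PNPLA3 elsewhere in that paragraph; this does not affect the present point.) Section 4.4 gives a calculated size of 28 and a final size of 30. Section 3 says "The first part of the study is conducted with 15 subjects", and section 4.4 uses those subjects to re-check the power calculation.

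Section 8.1 does not say which version of the Kolmogorov–Smirnov test is meant, whether it is applied to visit values or to within-subject changes, or which transformation follows a rejection.

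**The concern.** This is a stated rule that picks the scale of the primary analysis, so it is more than detail left for later. A non-significant pre-test leads to an untransformed analysis, yet with 15 to 30 values non-significance says little about normality.

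Expression and liver-fat values are positive and commonly right-skewed. On the raw scale a few subjects with high baseline values dominate the mean change, and power falls for the proportional effect on which the sample size is built.

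Two further consequences follow from the design. The gate can return one scale for the first 15 subjects and another for 30, and the first result informs whether 15 more people are enrolled. Under section 8.2 each transcript, metabolite or taxon can land on its own scale, so effect sizes are not comparable across features.

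**Working it through.** **The plan's own figure.** The protocol states no operating characteristic for the pre-test. Its one related figure, 28 subjects for 80% power at two-sided 0.05, cannot be reproduced because no SD or proportions are given. A one-sample t-test with n=28 would need a standardised effect of 0.549, so a 25% reduction implies an SD of change of 0.25/0.549 = 45.5% of baseline. The sample size therefore does not supply the variability needed here.

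**Inputs from the protocol.** n = 15, 28 and 30; effect ratio 0.75; one-sample t-test on change; Kolmogorov–Smirnov gate.

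**Inputs assumed.** Log-normal values with log-SD σ = 0.5–0.9. The coefficient of variation is √(exp(σ²) − 1), so 0.53 at σ = 0.5 and 1.12 at σ = 0.9. Within-subject correlation ρ on the log scale is 0.3–0.8.

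**Step 1: critical values.** The statistic is D = max |Fₙ(x) − Φ((x − x̄)/s)|, where Fₙ is the empirical distribution function. The 5% critical values are:

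| n | Mean and SD known in advance | Mean and SD estimated (Lilliefors) |
| --- | --- | --- |
| 15 | 0.338 | 0.219 |
| 28 | 0.250 | 0.164 |

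If estimated values are read against the first column, the true size is below 0.1% instead of 5%.

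**Step 2: how often skewness is missed (σ = 0.7, visit values).**

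| n | Uncorrected | Lilliefors |
| --- | --- | --- |
| 15 | 97% | 57% |
| 28 | 88% | 30% |

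**Step 3: power on the log scale, checked by hand.** The log ratio has mean ln 0.75 = −0.288 and SD σ√(2(1 − ρ)). At σ = 0.7 and ρ = 0.8 the SD is 0.7 × √0.4 = 0.443, so the standardised effect is 0.288/0.443 = 0.65. The noncentrality is 0.65 × √15 = 2.52 at n=15 and 0.65 × √28 = 3.44 at n=28. These agree with the simulated 65% and 91% below.

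**Step 4: power of the gated procedure (simulation, 20,000 trials per setting, visit values tested).**

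| σ | ρ | n | Uncorrected gate | Lilliefors gate | Log always | Loss, uncorrected |
| --- | --- | --- | --- | --- | --- | --- |
| 0.5 | 0.3 | 15 | 37% | – | 42% | 5 |
| 0.5 | 0.8 | 28 | 98.5% | – | 99.6% | 1.1 |
| 0.7 | 0.8 | 15 | 51% | 62% | 65% | 14 |
| 0.7 | 0.8 | 28 | 83% | 90% | 91% | 8 |
| 0.9 | 0.8 | 15 | 31% | – | 45% | 14 |
| 0.9 | 0.8 | 28 | 64% | – | 74% | 10 |
| 0.9 | 0.3 | 28 | 26% | – | 28% | 2 |

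If the uncorrected gate is applied to differences at σ = 0.9 and n=28, power is 58% against 74%, a loss of 16 points. With Lilliefors the loss is 0–3 points when visit values are tested and 1–7 points when differences are tested.

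**Step 5: a second, independent simulation (40,000 replicates, gate on changes, ρ = 0.7).**

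| σ | n | Raw | Uncorrected gate | Lilliefors gate | Log always |
| --- | --- | --- | --- | --- | --- |
| 0.5 | 15 | 68% | 68% | 71% | 76% |
| 0.5 | 28 | 93% | 93% | 95% | 97% |
| 0.75 | 15 | 31% | 32% | 38% | 43% |
| 0.75 | 28 | 54% | 58% | 67% | 71% |

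**Step 6: type I error.** The raw-scale t-test has 3.1–4.9% and the log-scale test 4.8–5.2%. Neither is materially above 5%.

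**The case against.** The strongest objection is that the harm depends on a version of the test that the protocol does not name. A reader might infer from section 8.1 that the null is a fully specified normal and that the gate almost never rejects. The document does not support this. It names only the test and SPSS, and an analysis with the Lilliefors correction fits the text equally well. At σ = 0.7 the corrected test detects the skewness in 43% of samples at n=15 and 70% at n=28. Even the uncorrected test rejects in 16% and 38% of samples at n=28 when σ is 0.75 and 1.0. This objection stands, and both versions are therefore reported above.

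The size of the loss is also not anchored in the protocol, which gives no SD, skewness or correlation. With mild skewness (σ = 0.3–0.5) the loss is only 0–7 points. This stands too.

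A reader might also suspect false positives. The calculations do not show any: the cost is power and a stable scale.

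The log scale is not free either. It changes the target from the arithmetic mean change to a ratio of geometric means, and if the truth is additive and normal it costs up to about 6 points of power.

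Finally, the version of the test and the transformation could be left to an analysis plan. That answers the missing detail, but it does not answer the rule itself. Section 8.1 already makes a weak pre-test decide the scale, and naming the version would reduce the loss without removing the data-dependent choice.

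**Conclusion.** The point holds in a limited form. At 15 to 30 subjects the analysis scale is chosen by a pre-test that often misses skewness under either version, most clearly at n=15, while the planned effect is proportional. For log-normal data with log-SD 0.5–0.9 and correlation 0.3–0.8, the power loss against a prespecified log scale is about 1–16 points if the test is uncorrected and about 0–7 points with Lilliefors. The direction is consistent across the two simulations, but the size rests on assumed variability and on the unstated version of the test. Validity is not threatened. The change is worth making before the 15-subject analysis, because a scale chosen after seeing those data would itself be data-driven.

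**What to change.** In section 8.1, remove the pre-test as the rule that picks the scale, and state in advance:

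- Gene expression, and other positive ratio-scale outcomes such as MRS liver fat and metabolite concentrations, are analysed as within-subject log ratios with a one-sample t-test. Results are reported as percent change with a 95% confidence interval, and a rule for zero values is given.
- Ordinal histology scores are compared with a paired rank test. The named Mann-Whitney fallback is for independent groups and does not suit baseline-to-endpoint data.
- Any normality check (Q-Q plot or Shapiro–Wilk) is applied to the within-subject differences, as a sensitivity diagnostic only.
- Section 8.2 refers to the same fixed scale, and the 15- and 30-subject analyses both use it.

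The cost is wording only, with no extra subjects, biopsies or data. The target becomes a ratio of geometric means, which suits the percentage target in section 4.4, and a few points of power are lost if the truth is additive and normal.

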# METHODS

## Study parameters/endpoints

### Main study parameter/endpoint

Main study parameters and endpoints include:

- NAFL disease progression, evaluated by liver biopsy and MRI/MRS scan. This is based on analysis between baseline and endpoint.
- Hepatic, muscle and adipose tissue histology and gene expression (evaluated by RNA-sequencing) that is affected by exercise intervention. This is based on liver, muscle and adipose tissue biopsy at baseline and endpoint.

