## Randomisation, blinding and treatment allocation

Not applicable.

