## Secondary study parameter(s)

Metabolome, transcriptome and microbiota data will be analysed as stated above.

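### Section 8.1 names Mann-Whitney as fallback, and an unqualified chi-square test, for within-subject comparisons: where these are used the pairing is ignored and power is lost

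*Protocol*

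**What the plan says.** The Study Design section describes one group: "This study is designed as an intervention study in which subjects will follow the 12-week exercise intervention". The section on randomisation, blinding and allocation reads "Not applicable". For the tissue parameters, section 6.1.1 says: "This is based on liver, muscle and adipose tissue biopsy at baseline and endpoint". Each endpoint value therefore has a baseline partner from the same person, and there is no second group.

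Section 8.1 says the primary analyses will be "performed between the baseline and endpoint intervention by analysis of one-sample t-test, or chi-square test". Data that fail a Kolmogorov-Smirnov check are to be transformed. After that: "If the data is not normally distributed and data transformation is not possible, the Mann-Whitney test will be used". The section closes with "Further associations will be assessed with Pearson rank correlation test / Pearson chi-square test". Section 8.2 extends the same rules: "Metabolome, transcriptome and microbiota data will be analysed as stated above". The protocol names no paired rank test and no paired categorical test.

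**The concern.** Mann-Whitney treats the baseline and endpoint values as coming from two unrelated sets of people. A Pearson chi-square on a visit-by-category table does the same. When a subject's two values are positively correlated, both tests use a variance that is too large for the change being tested, so a real within-subject change is harder to detect.

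The outcomes most likely to reach these tests matter to the study. Liver histology is among the main parameters, and a graded or categorical reading cannot be transformed to normality. Through section 8.2, sparse microbiota data can follow the same route. Subjects have liver, muscle and fat biopsies at both visits, and a test that discards the pairing wastes part of that information. The first 15 subjects also feed the interim look that informs whether to recruit 15 more.

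This is not a detail left to a later analysis plan. The protocol names specific tests, and an analysis plan that followed it would carry the mismatch forward.

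**Working it through.** **1. The plan's own figure.** Section 4.4 gives n=28 for a 25% reduction in expression (two-sided chi-square, alpha 0.05, power 0.80). It states no baseline proportion, SD or within-subject correlation, and expression is continuous, so 28 cannot be reproduced. The two-proportion formula gives 27 per group only at the extremes (1.00 to 0.75, or 0.25 to 0.00). The other baselines tried gave 36 to 62 per group for an absolute 25-point drop and 38 to 686 for a relative drop. There is thus no verified planned power to measure a loss against.

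**2. Reference effect (assumption).** A paired t-test has 80% power at n=28 when the standardised change (mean change / SD of change) is 0.549. For a 25% reduction, this means an SD of change of 25/0.549 = 45.5% of the baseline mean. This value is back-solved and is not stated in the plan.

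**3. Why pairing matters.** Let each visit have SD s.
- True variance of the mean change: 2s²(1 − rho)/n.
- Variance assumed by an independent-samples test: 2s²/n.
- The test statistic therefore has a true SD of √(1 − rho) instead of 1.

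For a two-sample z-test this gives:
- true type I error = P(|Z| > 1.96/√(1 − rho));
- power ≈ P(Z > 1.96/√(1 − rho) − 0.549√n).

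At rho=0.5 and n=28, 1.96/√0.5 = 2.77 and 0.549 × √28 = 2.91. Type I error is about 0.6% and power about 55%. Mann-Whitney behaves similarly but not identically, so it was simulated.

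**4. Simulation.** Bivariate normal pairs, 20,000 runs per setting, Mann-Whitney against Wilcoxon signed-rank, nominal two-sided 5%. Rho is not in the documents, so a range is shown.

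| n | rho | Mann-Whitney power | Signed-rank power | Mann-Whitney type I error |
|---|---|---|---|---|
| 28 | 0 | 79% | 78% | 4.8% |
| 28 | 0.3 | 67% | 78% | 1.9% |
| 28 | 0.5 | 49% | 77% | 0.8% |
| 28 | 0.7 | 23% | 77% | 0.2% |
| 15 | 0 | 50% | 46% | 4.4% |
| 15 | 0.3 | 35% | 46% | 2.0% |
| 15 | 0.5 | 22% | 46% | 0.8% |
| 15 | 0.7 | 9% | 47% | 0.1% |

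Signed-rank type I error was 4.6-4.7% at n=28 and 3.9-4.2% at n=15. Repeat runs differed by 1 to 3 points.

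**5. Categorical outcomes.** The protocol defines no binary main endpoint, so these inputs are illustrative.
- No change (0.60 at both visits, n=28): Pearson chi-square rejects in 4.8% of samples at rho=0, 0.5% at rho=0.5 and 0.06% at rho=0.7.
- A fall from 0.60 to 0.35 with rho=0.5, n=28: power is 43% for chi-square, 62% for exact McNemar and 77% for asymptotic McNemar.
- The same fall at n=15: 19% for chi-square and 16% for exact McNemar. Rerunning these inputs with mid-p McNemar gives about 30% at n=15 and 74% at n=28.

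**The case against.** The strongest objection is that the table describes a test the plan reaches only as a last resort. Section 8.1 starts with a one-sample t-test, then a transformation, and only then Mann-Whitney. Following that whole sequence on paired lognormal data (log-SD 0.5 and 1.0, rho 0.3 to 0.7, standardised change 0.549, 3,000 runs), Mann-Whitney was reached in about 2-5% of samples. Overall power was 73-76% at n=28 against 77-79% for signed-rank, and 44-48% at n=15 against 47-50%. Type I error stayed at 4.1-5.5%. This stands. For skewed continuous outcomes that a log transform repairs, such as expression, the practical loss is small. A reader might infer from the table that much of the study's power is lost overall, and the documents do not support that.

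Other limits also stand:
- A reader might take a wrong test to mean false positives. With positive rho the error runs the other way, and at rho=0 there is no loss.
- The first chi-square mention does not say which test. McNemar is itself a chi-square test, so that wording is unspecific rather than certainly wrong.
- The correlation sentence concerns associations between variables, where Pearson methods can be valid. Calling a Pearson correlation a rank test is a naming slip and not a pairing error.
- A reader might go on to say that the Kolmogorov-Smirnov check makes the choice of test close to arbitrary, or that a log transform must be fixed in advance. The check is weak at n=15, but a check that rarely rejects sends data to the valid t-test. These are preferences, and such detail can sit in an analysis plan.

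The objection does not rescue the fallback. Graded histology readings cannot be transformed to normality, and the loss also appears in simulated four-level ordinal scores. Nothing in the protocol makes Mann-Whitney right for paired data.

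**Conclusion.** The point holds in limited form. Mann-Whitney does not fit a single-arm baseline-endpoint comparison, and neither does chi-square if run as Pearson chi-square between visits. The one-sample t-test on within-subject change does fit. The mismatch therefore affects only outcomes that reach the fallback or the categorical test.

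For those outcomes the consequence is conservative inference. Under the assumed change of 0.549, Mann-Whitney gives up about 11 or 12 points of power at rho=0.3, 28 at rho=0.5 and 54 at rho=0.7 with n=28, and nothing at rho=0. These sizes rest on normal data, an effect back-solved from a paired t-test, and a correlation the protocol does not give. They are conditional on the fallback being used and do not measure a shortfall in the study's overall power.

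**What to change.** Amend section 8.1 as follows; section 8.2 then inherits the change.

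- State that the one-sample t-test is applied to within-subject change from baseline to endpoint.
- Replace Mann-Whitney by the Wilcoxon signed-rank test for continuous and ordinal outcomes.
- For categorical baseline-endpoint comparisons, name McNemar for binary outcomes and a marginal homogeneity test for more than two categories. Mid-p McNemar is preferable, since the exact version gains little over chi-square at n=15.
- Correct the rank correlation to Spearman, as a naming correction.

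The normality check and the transformation step can stay. The cost is a few lines of wording, with no change to data collection, visits or sample size.

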## Secondary study parameter(s)

Metabolome, transcriptome and microbiota data will be analysed as stated above.

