**Objective**: We aim to study the effect of exercise on NAFLD (by analysing hepatic lipid content, liver histology, and gene expression). Furthermore, we aim to establish the role of exercise-mediated changes in gut microbiome in the reduction of severity of NAFLD and the relation with other metabolically involved organs including adipose tissue and muscle metabolism and glucose excursions. We thus aim to identify biomarkers of exercise effect on NAFLD state. These biomarkers comprise plasma and urine metabolites, gene expression of liver, muscle and adipose tissue, as well as gut microbial composition.

**Study design:** Intervention study.

**Study population:** In total 15 subjects aged 18-70 years of age with diagnosed NAFLD.

**Intervention (if applicable)**: High-intensity interval exercise training for 12 weeks.

**Main study parameters/endpoints:** The main study parameters are changes in NAFLD liver histology and gene expression in relation to oral and gut microbiota composition changes upon exercise. Second changes in other organs involved upon exercise driven metabolic fitness including subcutaneous adipose tissue and muscle gene expression (RNA-sequencing) and histology, in relation to glucose metabolism (freestyle libre) and metabolites in plasma and urine will be studied. Finally, the relative contribution to NAFLD and glucose metabolism of the different organs (liver, adipose tissue and muscle) upon exercise will be studied.

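### Section 8.2 assigns RNA-seq, metabolome and microbiota data to single-variable tests with no multiplicity control, although gene expression in three tissues is a main endpoint

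*Protocol*

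**What the plan says.** Section 8.2 gives the whole method for the high-dimensional data in one sentence: "Metabolome, transcriptome and microbiota data will be analysed as stated above".

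What stands above it is section 8.1:

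- Software: "Statistical analyses will be performed by SPSS statistical analysis software".
- Main comparison: "The primary analyses of studied primary parameters will be performed between the baseline and endpoint intervention by analysis of one-sample t-test, or chi-square test".
- Fallback: "If the data is not normally distributed and data transformation is not possible, the Mann-Whitney test will be used".
- Associations: "Further associations will be assessed with Pearson rank correlation test / Pearson chi-square test".

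Section 8 gives no significance threshold, false discovery rate or family-wise control, and names no count-based or compositional model. The only alpha in the protocol is in section 4.4, for the sample size: "2sided chi- square test with a desired alpha of 0.05 and a desired power of 0.8".

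The data concerned are not peripheral. Section 6.1.1 lists among the main endpoints "Hepatic, muscle and adipose tissue histology and gene expression (evaluated by RNA-sequencing) that is affected by exercise intervention", and the Summary likewise puts liver gene expression among the main parameters.

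**The concern.** A protocol may leave the omics method to a later analysis plan. This one does not. It fixes the method as the tests of section 8.1, so an analysis plan that named a suitable RNA-seq model would depart from the protocol.

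Two things follow if the text is carried out as written. First, a test designed for one variable is repeated over thousands of genes with nothing to limit false calls, and the output is a list of genes said to respond to exercise and of candidate biomarkers. Second, the fallback test treats baseline and endpoint samples from the same person as two independent groups.

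The list also has a use inside the study. Under section 4.4, liver RNA-seq changes in the first 15 subjects inform whether 30 are needed, and a further 15 subjects would mean further baseline and endpoint biopsies.

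**Working it through.** The protocol gives no feature count, false discovery rate or expected number of false calls, so there is no figure of its own to reproduce.

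**Inputs**

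- Alpha 0.05, two-sided: section 4.4. Its use for the section 8 tests is an assumption.
- Three tissues: section 6.1.1.
- n = 15 in the first part, possibly 30 later: sections 3 and 4.4.
- Genes tested per tissue, m: not given. Assumed 10,000 to 20,000, with a wider range shown.
- One test per gene: assumed.

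**t-test route**

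Expected false positives = m × π0 × 0.05, where π0 is the share of genes that do not change.

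| m per tissue | all null | 80% null |
|---|---|---|
| 5,000 | 250 | 200 |
| 10,000 | 500 | 400 |
| 15,000 | 750 | 600 |
| 20,000 | 1,000 | 800 |
| 40,000 | 2,000 | 1,600 |
| 60,000 | 3,000 | 2,400 |

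For 10,000 to 20,000 genes in each of three tissues, the all-null total is 3 × 500 to 3 × 1,000 = 1,500 to 3,000. The simulated size of the paired t-test at n = 15 was 0.048 to 0.053, so the nominal 0.05 is a fair input.

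For smaller data layers such as metabolites or taxa, whose counts are also not given, 100 to 1,000 features would yield 5 to 50 false calls if nothing changes.

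**Mann-Whitney route**

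Applied to positively correlated pairs, the test overstates the standard error and becomes conservative. Simulated at n = 15:

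| within-subject correlation | size | false calls, 10,000 to 20,000 genes |
|---|---|---|
| 0 | 0.043 | 433 to 866 |
| 0.3 | 0.022 | 221 to 442 |
| 0.5 | 0.006 | 60 to 120 |

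Fewer false calls come at the price of power, since the test discards the pairing. Section 8.1 picks the route by a normality check, so the error rate would differ from gene to gene.

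**How much of the list would be false**

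This depends on how many genes really change. Simulation with m = 15,000, n = 15 and t-tests:

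| scenario | unadjusted 0.05 | Benjamini-Hochberg 5% |
|---|---|---|
| no gene changes | about 747 calls, all false | about 0.05 false calls |
| 5% of genes change by 1 SD | about 1,410 calls, 698 false (50%) | about 373 calls, 18 false (5%) |

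In the second scenario 750 genes truly change. Unadjusted testing finds about 1,410 − 698 = 712 of them and Benjamini-Hochberg about 373 − 18 = 355, so the control has a real cost in power.

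If instead 20% of the 15,000 genes change by 1 SD (power about 95%), unadjusted testing gives 12,000 × 0.05 = 600 false calls and 3,000 × 0.95 = 2,850 true ones. The false share is 600 / 3,450 = 17%.

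**The case against.** The strongest reply is that much of this rests on silence. Section 8 does not say that genes are tested one by one or that results stay unadjusted, and it sets no threshold. The false discovery rate level and normalisation are often left to an analysis plan, which may exist. Section 6.1.3 describes one RNA-seq analysis as pathway-based, which would mean far fewer tests. Section 8.1 allows transformation, which could include a log-ratio step for taxa. The first part is a 15-subject pilot looking for potential biomarkers, where some false leads are tolerable. This stands as far as the numbers go: they are conditional and should be quoted with their assumptions. It does not remove the defect, because section 8.2 names the tests and the fallback is wrong for paired data whatever threshold is used.

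Four stronger readings are tempting, and the document does not support them:

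- **Thousands of false genes per tissue.** At 10,000 to 20,000 genes the figure is 500 to 1,000. Thousands needs about 40,000 or more features per tissue, or summing over three tissues. It does not apply on the Mann-Whitney route.
- **A list made up mostly of noise.** That is so if few genes respond. The false share was 50% with 5% of genes changing and 17% with 20% changing.
- **Midway samples left unused.** Section 8.1 ties the baseline-to-endpoint comparison to primary parameters, and section 6.1.2 bases microbial composition and blood metabolites on three visits. The samples are in the plan. What is missing is a test that handles three time points, since none of the comparison tests named does.
- **Hepatic PNPLA3 as the one confirmatory test because it was sized.** Section 4.4 argues from PNPLA3 but states the 25% reduction for PNPLA2. That contradiction must be reconciled before any gene is singled out.

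**Conclusion.** The concern holds in a bounded form. Section 8.2 fixes an unsuitable method for data that include a main endpoint: single-variable tests, an unpaired fallback for paired samples, and no stated control of multiplicity.

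If genes are tested individually at 0.05 and 10,000 to 20,000 are tested per tissue, the t-test route yields about 500 to 1,000 false positives per tissue when nothing changes and 400 to 800 when 80% of genes are null. The Mann-Whitney route yields about 60 to 440 at within-subject correlations of 0.3 to 0.5, with loss of power. The gene count, the gene-wise testing and the use of 0.05 in section 8 are assumptions. The choice of tests and the absence of any stated control are in the text.

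**What to change.** Replace the sentence in section 8.2 with the following:

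- For RNA-seq, a paired model per tissue with subject as blocking factor (for example limma-voom, edgeR or DESeq2).
- Benjamini-Hochberg false discovery rate control at a stated level (for example 5%) within each tissue and each data layer.
- For taxa, a log-ratio transform before modelling.
- For stool, oral and blood measures taken at baseline, midway and endpoint, a repeated-measures model using all three visits.

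In section 8.1, replace Mann-Whitney by the Wilcoxon signed-rank test for baseline-to-endpoint changes. Reconcile PNPLA3 and PNPLA2 in section 4.4 before naming any single gene as confirmatory.

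The cost is wording, plus software other than SPSS for the omics layers. No new data or visits are needed. The downside is that fewer features will be called: in the 5% scenario, about 355 instead of 712 of the 750 genes that truly change. The change is best made before the data from the first 15 subjects are analysed, because those results inform the decision to extend.
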